#### 2.6.2. Thematic Method

Thoughts and notes from the fieldwork constitute a preliminary analytical reflection on the material, further processing, and deepening in the actual analysis process [55]. The field notes of the observations will be analysed using an inductive thematic method [56], where the material is sorted and interpreted for the purpose of the study. The prominent themes will be analysed with the support of a theoretical framework, which depends on the focus of the material [57]. Participating researchers have extensive experience with ethnographic methods.

#### 2.6.3. Descriptive and Analytical Statistics

Descriptive and analytical statistics will be adapted to the data level and distribution. Furthermore, the Bayesian Repeated Measure ANOVA, performed within JASP Team (Version 0.16.4) [58], will evaluate whether there is any change over time regarding health-related quality of life, vision-related quality of life, and physical activity. Researchers with experience in statistical analysis will carry out the analyses. For a comprehensive description of the advantages of applying this analysis in our small sample study over more traditional analysis, see [59].

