## Abstract

Age-related macular degeneration (AMD) is the most common cause of incurable visual impairment and impacts daily life. These impacts include loss of social activities, decreased functional independence, and reduced physical activity. This protocol aims to describe a prospective, mixed-methodology for studying a population with AMD before, during, and after an empowerment-based physical activity intervention (EPI). A study framework was also developed for EPI. The intervention will include 20 older individuals (age 65+ years) with AMD recruited in Sweden. The intervention period is six months and comprises adapted physical activity and social activities in a group twice a week and individual health coaching on three occasions. The quantitative pre-test and three follow-ups include physical functional tests, an accelerometer that monitors physical activity continuously for one week, and questionnaires. Individual and focus-group interviews and ethnographic observations will explore the experience of living with AMD and what it means to participate in the EPI for individuals with AMD. The chosen methodology offers a structured way for researchers to explore the experiences and factors that may provide insights into the potential of creative supervised, adapted physical activity in groups, health coaching, and socialising that are significant to enable well-being among older individuals with AMD.

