### 2.5. Data Collection and Data Sources

Data will be collected before, during, and after the intervention with varying data sources (Figure 1):

Individual qualitative interviews with open-ended questions will be performed before the participants join the intervention, and ethnographic observations will be performed during the intervention. After the intervention ends, focus-group interviews will be performed with the participants (after six months).

Quantitative baseline data will be collected from recruited participants, including demographic data (age, sex, marital status, and housing). A test protocol for the quantitative data is used for the data collection at baseline, at four months, at the end of intervention at six months, and 12 months after the end of the intervention. The protocol comprises physical functional tests for the assessment of strength with the Sit and Stand Test (i.e., 30STS), Time Up and Go (TUG), and an accelerometer (3-axis accelerometer) worn for one week. Questionnaires for the self-reported assessment of visual functioning/vision-related quality of life (i.e., NEI VFQ-25), health-related quality of life (i.e., EQ-5D-5L), physical activity (i.e., PASE), and self-efficacy for exercise (i.e., EXSE) are included in the test protocol.

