A limitation of the planned study is that the findings will represent a small sample of respondents. A potential risk to the project implementation is the health status of the participants, as they are older people with impaired vision and possible co-morbidities. However, one of the purposes of empowerment-based physical activity is to adapt the activities to individual participant conditions, hopefully decreasing the drop-out rate during the project period. There is also the risk of the loss to follow-up becoming considerable. Thus, the primary endpoint of the trial is at the end of the intervention at six months, as the longer follow-up at 12 months after the end of the intervention poses a risk of a high proportion of missing data.

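### Section 2.6.3 does not say which visits enter the repeated-measures ANOVA; if all four do, missing data at the last visit would shrink the six-month comparison

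*Protocol article*

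**What the plan says.** Three places in the protocol article bear on this.

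- **Visits (2.5, Data Collection and Data Sources).** The quantitative tests and questionnaires are done "at baseline, at four months, at the end of intervention at six months, and 12 months after the end of the intervention". That makes four visits, the last at month 6 + 12 = 18.
- **Analysis (2.6.3, Descriptive and Analytical Statistics).** For health-related quality of life, vision-related quality of life and physical activity, "the Bayesian Repeated Measure ANOVA, performed within JASP Team (Version 0.16.4) [58], will evaluate whether there is any change over time". The section does not list the visits that enter the model and describes no separate six-month contrast. A general clause precedes this: "Descriptive and analytical statistics will be adapted to the data level and distribution".
- **Primary time point (3, Discussion).** The text warns: "There is also the risk of the loss to follow-up becoming considerable". It then says that "the primary endpoint of the trial is at the end of the intervention at six months", giving as the reason that "the longer follow-up at 12 months after the end of the intervention poses a risk of a high proportion of missing data".

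The sample is small (Abstract): "The intervention will include 20 older individuals (age 65+ years) with AMD recruited in Sweden".

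**The concern.** The Discussion chooses six months so that the main result does not depend on a visit that many participants may miss. That protection works only if the six-month analysis is computed without needing the last visit.

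A repeated-measures ANOVA in its standard form takes one complete row per participant, with one column per visit. Anyone with an empty cell is left out of the whole model, including the comparisons between visits that they did attend. Section 2.5 lists four visits under one test protocol, and 2.6.3 speaks of change over time without limiting the visits. The natural reading is therefore one model over all four. On that reading, a participant seen at baseline, four and six months but not at month 18 drops out of the baseline-to-six-month comparison.

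With 20 participants, each exclusion costs noticeable precision. The six-month result would also describe only those who stayed for 18 months, who may differ from those who completed the intervention.

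**Working it through.** The plan gives no power calculation, standard deviation, effect size or loss rate, so there is no stated figure to reproduce. The check asks what follows if all four visits enter one complete-row model.

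**Inputs from the document:** N = 20 (Abstract), four visits (2.5), six months primary (Discussion).

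**Assumed inputs:** the numbers seen at six months and complete to month 18.

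**Step 1. Precision.** For a paired change with standard deviation SD, the 95% half-width is t(0.975; n−1) × SD / √n. SD cancels in the ratio of two half-widths, so the baseline-to-six-month correlation does not matter.

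Assume 18 of 20 are seen at six months:

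| n in the six-month comparison | Half-width (in SD of the change) | Ratio to n = 18 |
|---|---|---|
| 18 (all seen at six months) | 2.110/√18 = 0.497 | 1.00 |
| 16 | 0.533 | 1.07 |
| 14 | 2.160/√14 = 0.577 | 1.16 |
| 12 | 2.201/√12 = 0.635 | 1.28 |
| 10 | 2.262/√10 = 0.715 | 1.44 |

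If instead all 20 are seen at six months, the reference half-width is 0.468. The ratios for n = 16, 14, 12 and 10 are then 1.14, 1.23, 1.36 and 1.53. If only 16 are seen at six months, the ratios for 14, 12 and 10 are 1.08, 1.19 and 1.34.

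**Step 2. Power, as a yardstick only, since the planned analysis is Bayesian.** For a two-sided 5% paired t-test, n = 20 gives 80% power at a standardised change of 0.66. At that same change, n = 16, 14, 12 and 10 give 69%, 63%, 55% and 46%.

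**Step 3. Behaviour with an incomplete last visit.** One simulated data set had 20 people and four visits, with 6 people missing only the last visit.

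- A standard repeated-measures ANOVA routine (not JASP) refused the data as unbalanced. Restricting to complete rows would drop all 6, although their six-month values exist.
- A random-intercept mixed model on all observations gave a standard error of 0.276 for the six-month change.
- The same model on the 14 complete cases gave 0.315, and 0.315/0.276 = 1.14.

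**Step 4. Possible bias, entirely conditional.** Assume 35% loss at month 18, a true six-month change of zero, equal correlation between visits, and log-odds of loss rising by 0.5 or 1.0 per SD of poorer six-month change. A simulation of 400,000 draws gives a complete-case overstatement, in outcome SD, of:

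- 0.128 (slope 0.5) or 0.227 (slope 1.0) at correlation 0.7;
- 0.165 (slope 0.5) or 0.292 (slope 1.0) at correlation 0.5.

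The upward direction is built into the assumption about who leaves.

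**Step 5. The alternative reading.** If the primary model uses only baseline, four and six months, nobody is removed because of the last visit, and Steps 1 to 4 do not apply.

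**The case against.** The strongest reply is that the document never says all four visits enter one model. Section 2.5 lists when data are collected, not what is modelled. A model on visits up to six months fits both 2.6.3 and the Discussion. The visits in a model and the handling of incomplete participants are also details that a condensed article may leave to a fuller plan. This stands in part: the point must be conditional, and the absence of a missing-data strategy is not itself a fault here. But the article does name the method, the software version and the reason for the primary time point, and on the natural reading the method works against that reason. The clause on adapting statistics concerns measurement level and distribution, so it does not settle the matter.

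A reader might go further and infer that the plan requires complete data at all four visits, that it expects heavy loss, and that its six-month estimate is therefore biased upward. The documents do not support this:

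- No requirement of completeness is stated.
- The Discussion speaks of a risk, gives no rate, and hopes that adapting activities will limit drop-out.
- Nothing shows who would be lost, so the direction of any bias is unknown.
- How JASP 0.16.4 treats a missing visit is not described and was not tested. Exclusion of incomplete rows is a general property of the standard method.

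It is also fair that this is a single-group study with a qualitative core, that it admits its small sample as a limitation, and that other paired analyses are not excluded. This lowers the weight of the point but does not remove it.

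**Conclusion.** The point holds in conditional form. Section 2.6.3 leaves open which visits enter the repeated-measures ANOVA. If all four do and the model uses complete rows, loss at month 18 reduces the six-month comparison that the Discussion meant to protect.

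Its size depends on loss rates that the documents do not give. With 18 of 20 seen at six months and 14, 12 or 10 complete at the last visit, the interval for the six-month change is about 16%, 28% or 44% wider. This loss of precision needs no assumption about who leaves. An upward bias would arise only if those lost had a poorer six-month change, and the 0.13 to 0.29 outcome SD found by simulation illustrates that assumption and is not an estimate for this study.

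The point is worth fixing before results are seen but is not critical, and confidence is moderate.

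**What to change.** Change 2.6.3 in one of two ways.

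1. **Preferred.** Replace the ANOVA with a Bayesian linear mixed model: visit as a categorical effect, a random effect for participant, and all available observations. Report the baseline-to-six-month contrast as primary. Participants who miss only the last visit then still contribute their six-month data.
2. **If the ANOVA is kept.** State that the primary model uses baseline, four and six months only, and analyse the visit 12 months after the end of the intervention separately as secondary. This still leaves out anyone who misses the four-month or six-month visit.

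If the second option is what the team already intends, one sentence naming the visits settles the point. The cost is a change of wording and a little more analysis work, with no new data or participants.

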## 3. Discussion

The study will be an example of a mixed-method study comprising a multi-case intervention study with qualitative and quantitative analyses but with a qualitative core component. The study protocol, with multiple data sources, is significant for fully capturing the various aspects of what it means to have AMD and generating a comprehensive understanding of the impact of participating in an empowerment-based intervention. EPI includes a participatory strategy and involves the participants in the choices of activities, listening to their needs. The intervention also acknowledges the need for expert opinion and theory in the empowerment and health promotion field to design the intervention. This strategy is essential to Reflective Equilibrium Community Empowerment, which takes advantage of top-down and bottom-up approaches [35].

The bottom-up approach in EPI entails that the participants will be allowed to have as much control as possible over the activities they are involved in and is an essential part of an empowerment process [39]. Since the participants will be coached at the beginning of the intervention, we will be able to adapt the intervention to the participants’ local environment and social context and understand their specific reality. This can contribute to a better condition for effective authorisation [60,61,62]. Empowerment is also seen as a key strategy for sustainable health promotion efforts.

The results of this project will fill a gap in the research literature and may provide insights into the potential of creative supervised, adapted physical activity, health coaching, and socialising. Thus, EPI might increase physical activity and strength and reduce sedentary behaviours for older people with AMD. The social part of the EPI is also aimed at supporting the participants in changing their social lives. This can be particularly important after a pandemic when older people have been isolated for a long time. The EPI is also aimed at strengthening their participation in existing municipal group training for older people, sports movement activities, and the Parasport Association’s activities after completion of EPI, resulting in a sustainable solution for the participants. Thus, EPI could improve the health-related determinants of daily life.

A limitation of the planned study is that the findings will represent a small sample of respondents. A potential risk to the project implementation is the health status of the participants, as they are older people with impaired vision and possible co-morbidities. However, one of the purposes of empowerment-based physical activity is to adapt the activities to individual participant conditions, hopefully decreasing the drop-out rate during the project period. There is also the risk of the loss to follow-up becoming considerable. Thus, the primary endpoint of the trial is at the end of the intervention at six months, as the longer follow-up at 12 months after the end of the intervention poses a risk of a high proportion of missing data.

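### The primary endpoint is set at six months with no outcome named, but the only named inferential method asks about change at any time and is not tied to six months

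*Protocol article*

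**What the plan says.** Three places in the protocol article bear on this.

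- **Discussion (limitations paragraph).** "Thus, the primary endpoint of the trial is at the end of the intervention at six months". The reason given is that "the longer follow-up at 12 months after the end of the intervention poses a risk of a high proportion of missing data". No outcome variable is named with the time point.
- **Section 2.5.** The quantitative test protocol is applied "at baseline, at four months, at the end of intervention at six months, and 12 months after the end of the intervention". That is months 0, 4, 6 and 18 (6 + 12).
- **Section 2.6.3.** "Descriptive and analytical statistics will be adapted to the data level and distribution". The section then adds the one method it names: "the Bayesian Repeated Measure ANOVA, performed within JASP Team (Version 0.16.4) [58], will evaluate whether there is any change over time". It applies this to three domains: health-related quality of life, vision-related quality of life and physical activity. Physical activity is itself measured in two ways, by accelerometer (2.5.5) and by PASE (2.5.8).

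Section 2.6.3 does not mention six months, does not list the visits that enter the ANOVA, and states no Bayes-factor threshold.

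**The concern.** The article makes two choices that do not meet. One fixes when the primary result is read. The other fixes the question the inferential analysis answers, and that question concerns the whole time course.

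The time effect of a repeated-measures ANOVA measures how far the visit means spread around their average. A rise at month 4 that has gone by month 6 produces it. So does a fall after the programme ends. Because it works on squared deviations, it treats a rise and a fall of the same size alike.

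In a single group of 20, a time effect could therefore be reported as the result of the programme although nothing differed between baseline and six months. Because no outcome is ranked first among three domains, whichever one shows such an effect could be put forward afterwards.

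**Working it through.** **Inputs from the article.** N = 20 in one group (Abstract); visits at months 0, 4, 6 and 18 (2.5); primary time point month 6 (Discussion); analysis question and method (2.6.3). The article gives no power, SD, correlation or threshold, so there is no figure of its own to reproduce.

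**Assumptions.** Equal within-person correlation ρ of 0.5, 0.7 or 0.8 between visits; SD 1; complete data; a 0.5 SD shift at one visit only. An omnibus result counts as positive if the F test has p < 0.05 or, closer to the named method, if a JZS Bayes factor for time (fixed-effect scale 0.5) exceeds 3. The comparator is a paired six-month-minus-baseline contrast at p < 0.05.

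**Analytic check of the F test.** With k visits and shift d at one visit, the sum of squared deviations of the visit means is d²(1 − 1/k). The noncentrality is

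λ = N·d²(1 − 1/k)/(1 − ρ), with k − 1 and (N − 1)(k − 1) degrees of freedom.

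- Four visits: λ = 20 × 0.25 × 0.75/(1 − ρ) = 3.75/(1 − ρ), which is 7.5, 12.5 and 18.75. With 3 and 57 degrees of freedom the power is 59%, 83% and 95%.
- Three visits (0, 4, 6): λ = 20 × 0.25 × 0.667/(1 − ρ) = 3.33/(1 − ρ), which is 6.67, 11.11 and 16.67. With 2 and 38 degrees of freedom the power is 60%, 83% and 95%.

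Neither the sign of the shift nor the visit at which it occurs enters λ.

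**Simulation, four visits, 10,000 data sets per row.**

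| True pattern | ρ | F test p < 0.05 | Bayes factor > 3 | Six-month contrast p < 0.05 |
|---|---|---|---|---|
| No change | 0.5 / 0.7 / 0.8 | 5.3 / 4.8 / 4.6% | 1.9 / 1.7 / 1.5% | 5.1 / 4.9 / 4.6% |
| +0.5 SD at month 4 only | 0.5 / 0.7 / 0.8 | 59.4 / 83.4 / 95.5% | 41.5 / 69.5 / 89.0% | 5.0 / 4.8 / 5.0% |
| −0.5 SD at month 18 only | 0.5 / 0.7 / 0.8 | 59.8 / 83.0 / 95.5% | 41.9 / 69.0 / 89.1% | 5.4 / 4.8 / 5.1% |
| +0.5 SD at month 6 only | 0.5 / 0.7 / 0.8 | 58.7 / 83.3 / 95.5% | 41.3 / 69.6 / 89.1% | 56.1 / 78.2 / 91.5% |

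The last three patterns give practically the same omnibus rates. Only the contrast tells the six-month effect apart from the other two.

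**Sensitivity to the correlation pattern.** If correlation decays with time (12-month correlation 0.4 to 0.6), a 0.5 SD fall at month 18 makes the F test positive in 56% to 72% of runs, or 47% to 63% with Greenhouse-Geisser correction. A 0.5 SD rise at month 4 does so in 67% to 91%, or 53% to 79% corrected.

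**Precision of the six-month change.** The 95% half-width is t × √(2(1 − ρ)/n). For n = 20, t = 2.093, giving 0.47, 0.36 and 0.30 SD at ρ = 0.5, 0.7 and 0.8. If the analysis kept only people seen at every visit and 14 of 20 remained (both assumed), t = 2.160 and the half-widths would be 0.58, 0.45 and 0.37 SD.

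**The case against.** The strongest reply is that 2.6.3 is one short paragraph of a journal article, and that contrasts, credible intervals and the covariance model normally sit in an analysis plan that is not shown. The study also describes its core as qualitative, admits its small sample, and states no decision rule. This stands as far as missing detail goes, and no fault is found with that. It does not remove the mismatch: the article itself declares a primary time point and itself states the analysis question, and the two differ.

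Three stronger readings are tempting, and the article does not support them.

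- **That the plan yields no six-month estimate.** Descriptive statistics are also planned, and a fitted repeated-measures model can give estimates by visit. The fair statement is that the article commits to none.
- **That the ANOVA certainly uses all four visits.** This is inferred from the visit schedule; 2.6.3 does not say so. If only months 0, 4 and 6 enter, the month-18 scenario falls away. The month-4 scenario stays at 60% to 95% for the F test.
- **That the uneven visit spacing invalidates the error term.** The article specifies no covariance model, and uneven spacing alone does not prove unequal variances of differences. Under the decaying correlations assumed above, pooling would overstate the standard error of the six-month contrast. That makes the contrast conservative and does not produce false positives.

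**Conclusion.** The point holds as a mismatch between two stated items: a six-month primary endpoint with no outcome, and a non-directional time effect in three domains that is not tied to six months. This follows from the wording and needs no simulation.

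Its size does depend on assumptions. With N = 20, no six-month change, a 0.5 SD shift at one other visit and constant correlation of 0.5 to 0.8, the omnibus F test is positive in about 59% to 96% of trials and the JZS Bayes factor exceeds 3 in about 41% to 89%. The six-month contrast is positive in about 5%. The correlations, the shift and both thresholds are not in the article. Decaying correlation lowers most of these rates but leaves them far above 5%. It should be corrected, and the correction is small.

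**What to change.** In 2.6.3:

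1. Name one primary outcome. Which one is the sponsor's choice; the NEI VFQ-25 composite and PASE are candidates.
2. Make its change from baseline to six months the primary analysis, reported as posterior mean and 95% credible interval, using all participants seen at six months whether or not they attend the last visit. This keeps to the Discussion's own reason for choosing six months.
3. Report the all-visit time effect, the other outcomes, and the month-4 and month-18 changes as secondary. State which visits enter the ANOVA, and do not present its time effect alone as evidence of benefit.

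This takes a few sentences and no extra data. The downside is committing to one outcome in advance.
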